### Data collection

Data collection occurs at baseline, 3, 6, 12, 15 and 18 months via: in-person clinical assessments; cognitive testing; device-based monitoring; and online questionnaires administered through REDCap; and, process data collected in REDCap and by the health coach in REDCap health-coaching forms. Table 2 shows the timepoints at which each component of the data-collection occurs under the original, expanded, and COVID-adapted protocols. Table 3 and Additional file 9 provide extensive details of the objective and questionnaire measures, as well as their intended purpose in the trial (e.g., primary outcome, secondary outcome, process outcome). The data collection procedures used for each of these components are indicated below.

**Table 2 Tab2:** Data collection components and timepoint of collection

Data collection component		Timepoint					
		0 M	3 M	6 M	12 M*	15 M*	18 M*
Clinical assessment (in person)	Fasting venous blood draw ^a^	✓	✓	✓	✓		✓
	OGTT ^b^	✓	✓	✓	✓		✓
	Anthropometric ^b^	✓	✓	✓	✓		✓
	DXA ^b^	✓	✓	✓	✓		✓
	Blood Pressure ^b^	✓	✓	✓	✓		✓
	FMD ^b^	✓	✓	✓	✓		✓
	Cognitive Testing ^b^	✓		✓	✓		✓
Device-based monitoring	activPAL	✓	✓	✓	✓	✓	✓
	GT3X+	✓	✓	✓	✓		✓
	Activity Monitor Diary	✓	✓	✓	✓	✓	✓
Surveys (administered during clinic visit)	Health History Survey	✓					
	Medication Log ^a^	✓	✓	✓	✓		✓
	Allied Health Log ^a c^	✓	✓	✓	✓		✓
	OPTIMISE Survey ^a^	✓	✓	✓	✓	✓	✓
	Personal wearables questionnaire ^b c^	✓	✓	✓	✓		✓
	‘Typical 24 h’ Survey ^d^	✓	✓				
Surveys (self-completion)	Dietary intake questionnaire	✓	✓	✓	✓		✓
	Quality of Life Survey	✓	✓	✓	✓		✓
	Menstrual Status Questionnaire ^c^ (women only)	✓		✓	✓		✓
	Motivation for Physical Activity Survey ^c^	✓	✓	✓	✓		✓
	Motivation to Break Up Sitting survey ^c^	✓	✓	✓	✓		✓
	OPTIMISED Survey (delayed intervention) *					✓	✓
	COVID-19 impact questionnaire ^e^	✓		✓	✓	✓	✓
Implementation / intervention fidelity data	REDCap Metadata: instrument status, dates & times	✓	✓	✓	✓	✓	✓
	Fitbit usage		✓	✓	✓	✓	✓
	propelo™ message log: full record of all messages sent/received			✓	✓	✓	
	Health coaching forms		✓	✓			
	Tailoring forms			✓			
	Withdrawal and adverse events log ^f^	✓	✓	✓	✓	✓	✓

Abbreviations: *OGTT* oral glucose tolerance test, *DXA* dual energy x-ray absorptiometry; *FMD* flow-mediated dilation

* Expanded protocol only

^a^ Replaced with COVID-safe alternative during restrictions (self-completion questionnaire; self-report; no clinical visit, pathology visit HbA1c test only)

^b^ Dropped during COVID restrictions

^c^ Added part way through study

^d^ Subsample only - recruited first 30 participants, completed before expanded protocol began

^e^ Not timed with the assessments but triggered by events: soon after the Australian government implemented restrictions March 2020 (COVID-19 pandemic restrictions) or upon reporting of a withdrawal or adverse event

^f^ When reported

**Table 3 Tab3:** Clinical and device-based measures collected in the in-person visit clinical assessments

Component	Key constructs	Measures	
		Primary / secondary outcomes	Other measures
Fasting blood draws	Glycaemic control	Glycosylated haemoglobin (HbA1c %, HbA1c mmol/mol)*	
	Fasting glucose metabolism	Glucose and Insulin	
	Fasting lipid metabolism	LDL, HDL, Total cholesterol, Triglycerides	
	Inflammatory markers	Hs-CRP, TNF-α, IL-6, IL-1B, Adiponectin, Leptin	IFNy, IL-10, IL-12, IL-8, IL-4
	Neurotrophic factors	BDNF, IGF-1	NGF, VEGF-A
	Genetic risk factors		ApoE4
2 h Oral Glucose Tolerance Test	Postprandial metabolism of glucose & insulin	iAUC glucose, iAUC insulin, 2 h post-prandial glucose, 2 h post-prandial insulin	
Anthropometric	Body weight & body composition	Weight, waist circumference, DXA assessed total and regional fat mass, lean mass, total body fat percentage, DXA software estimated visceral adipose tissue mass	Height, BMI
Vascular	Blood pressure & heart rate	Resting systolic blood pressure, diastolic blood pressure, mean arterial pressure	Resting heart rate
	Flow Mediated Dilation	Post-deflation peak vessel diameter compared to resting diameter (FMD%)	Shear rate (cm/s), Shear rate AUC
Cambridge Neuropsychological Test Automated Battery (CANTAB)	Visual learning and new memory	Paired Associates Learning total errors (adjusted)^b^ (PAL TEA), PAL total errors 12 shapes (adjusted)	PAL total errors, PAL total errors 12 patterns
	Reaction Time	Reaction Time (RTI) simple median reaction time, RTI simple median movement time & RTI median 5-choice reaction time, RTI median 5-choice movement time	RTI simple error score (all), RTI total error score (5-choice)
	Visual matching ability and visual recognition memory	Delayed Matching to Sample (DMS) percent correct, DMS median correct latency	DMS total errors, DMS total correct (12 s delay)
	Working memory	Spatial Working Memory (SWM) between errors, SWM between errors (12 boxes), SWM strategy (6–12 boxes)	SWM total errors, SWM total errors (12 boxes)
Cognitive function	Global cognition		Addenbrooke Cognitive Examination-Revised (ACE-R) Mini Mental State Examination
Device-based monitoring (thigh-worn activPAL)	Sedentary behaviour	Overall sitting time^a^, Overall prolonged sitting time (≥30 min), Work sitting time, Work prolonged sitting time	
	Sedentary time accumulation	Usual bout duration, Alpha (overall and work)	
	Active breaks	Active breaks (n per day overall and work)	
	Physical activity	Standing, Stepping, LPA, MVPA (all overall and during work)	
	Sleep	Total sleep time, Sleep efficiency	Sleep onset latency, Wakefulness after sleep onset
Device-based monitoring (wrist-worn Actigraph GT3X+)	Sleep	Total sleep time, Sleep efficiency	Sleep onset latency, Wakefulness after sleep onset

Abbreviations: *ApoE4* Apolipoprotein E4, *BDNF* brain-derived neurotrophic factor, *BMI* body mass index, *CANTAB* Cambridge Neuropsychological Test Automated Battery, *DXA* Dual X-ray absorptiometry, *FMD* flow-mediated dilation, *HbA1c* Glycosylated Haemoglobin, *HDL* High density lipoprotein cholesterol, *Hs-CRP* High-specificity C-Reactive protein, *iAUC* incremental area under the curve, *IGF-1* insulin like growth factor 1, *IL-1B* interleukin-1 beta, *IL-6* interleukin-6, *LDL* Low Density Lipoprotein Cholesterol, *LPA* light intensity physical activity, *MVPA* moderate-vigorous intensity physical activity, *TNF-α* Tumour necrosis factor alpha

^a^Primary outcomes for original OPTIMISE protocol concerning diabetes (primary endpoint = 6 months)

^b^Primary outcome for expanded protocol concerning dementia (primary endpoint = 12 months)

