### Impact of the COVID-19 pandemic on the trial

Intensive lockdown restrictions occurred in March 2020 leading to the suspension of recruitment. All participants enrolled in the trial during these periods were assessed according to remote COVID-safe practices. In October 2020 the lockdown restrictions ended and resumption of recruitment and the expanded protocol began.

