#### Clinical assessment

Clinic visits occur at every data collection timepoint, wth the exception being at 15 months. Prior to each visit, participants are reminded to abstain from engaging in any moderate- to vigorous-intensity physical activity, from consuming caffeine and alcohol in the 24 h prior to the assessment, to fast for at least 8 h, and to take their medications for the day of the visit at lunchtime during the visit rather than in the morning. For each clinic visit, participants report to the Baker Institute Clinic at 8 am. Over a 5-h period, participants have their body weight, body composition, blood pressure and vascular function assessed, a fasting blood collection, and undergo a 2 h oral glucose tolerance test (OGTT) during which they complete their questionnaires*.* Upon completion of the OGTT, participants receive lunch (e.g., sandwich/coffee) followed by cognitive assessments. Those participants whose assessment occurs during COVID-19 related social isolation mandates are emailed the questionnaires and referred to off-site pathology for glycosylated haemoglobin (HbA1c) testing, all other measures are omitted.

Clinic measures and their procedures are described below.

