#### Statistical analyses

Outcomes are all continuous and expected to be either normal or log-normal, in which case log-transformation will be used. Analyses will be performed in STATA version 15 or higher. Significance is set at *p* < 0.05 two-tailed (except for *p* < 0.025 when testing co-primary outcomes based on α = 0.025). To test the differences between groups in primary and secondary outcomes during (3 months), end of the intervention (OPTIMISE; 6 months) and end of the extended maintenance phase (12 months – OPTIMISE-extended) mixed models statistical analysis will be employed, accounting for repeated measures, adjusting for baseline values, randomisation strata, and potential confounders. Within-group changes for intervention participants occurring during the no health coaching contact phase from 12 to 18 months will be tested and compared to intervention phases. Within-group changes will also be tested in the delayed intervention participants receiving the OPTIMISED intervention after 12 months, at the 18 month timepoint, using paired t-tests (or non-parametric paired tests). Possible confounders will be identified a priori from the literature and narrowed down to a number that can be modelled without overfitting, based on an objective criterion not open to manipulation (backwards elimination: retaining age, sex, and *p* < 0.2 association with the outcome). Analyses will follow intention-to-treat principles. Sensitivity to handling missing data will be evaluated by comparing results from the main analyses (evaluable case analysis for mixed models; complete-case analysis for t-tests) with alternative methods that are appropriate for different missing data scenarios (e.g., multiple imputation; selection-covariate adjustment). Descriptive statistics will be used to describe the implementation indicators of the different phases of the intervention.

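### COVID rules let a participant be randomised without a baseline PAL TEA score, and the main model as written would then drop that participant even if tested at 12 months

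*Protocol article*

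**What the plan says.** **Assessments under restrictions.** In Table 2 (Data collection) the footnote is attached to the row label, "Cognitive Testing ^b", and that row is ticked at 0, 6, 12 and 18 months. Footnote b reads "Dropped during COVID restrictions". It also covers the OGTT, anthropometry, DXA, blood pressure and FMD. The Clinical assessment section agrees: people assessed during isolation mandates are emailed questionnaires and "referred to off-site pathology for glycosylated haemoglobin (HbA1c) testing, all other measures are omitted". Neither place exempts the baseline visit.

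**Randomisation.** Under Study design and randomisation, allocation is automated at the end of the baseline assessment. The article states no requirement for a PAL TEA score.

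**Recruitment dates.** The COVID-19 section says "Intensive lockdown restrictions occurred in March 2020 leading to the suspension of recruitment", then "All participants enrolled in the trial during these periods were assessed according to remote COVID-safe practices", then "In October 2020 the lockdown restrictions ended and resumption of recruitment and the expanded protocol began". Methods/design, however, has recruitment to the extended 18-month trial starting in June 2020.

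**Analysis.** Between-arm differences at 3, 6 and 12 months are tested with mixed models, "accounting for repeated measures, adjusting for baseline values, randomisation strata, and potential confounders". The main handling of missing data is "evaluable case analysis for mixed models". Multiple imputation appears only as an example of a sensitivity analysis. Intention-to-treat principles are stated.

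**Power.** The Sample size section expects 80 per arm to complete 12 months and claims more than 80% power for PAL TEA at d = 0.33 (1/3 SD), r = 0.7, two-sided 5%.

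**The concern.** A likelihood-based mixed model copes with missing responses, but it cannot use a participant whose covariate is missing. If baseline PAL TEA is a covariate and the main analysis takes evaluable cases, someone randomised after a remote baseline visit contributes nothing to the primary cognitive comparison, even when tested in clinic at 6 and 12 months. That discards a randomised participant who has the primary outcome, for want of an adjustment variable, and sits badly with the intention-to-treat statement. The power calculation does not count this loss, because it counts 12-month completers rather than people with both scores. The same rule reaches the other footnote-b outcomes.

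**Working it through.** **Inputs.** From the Sample size section: n = 80 per arm, d = 0.33 (or 1/3), r = 0.7, two-sided 5%. Assumed, because the article gives no figure: the share m of 12-month completers without a baseline score, taken as 5%, 10% and 20%.

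**Step 1: reproduce the planned power.** In SD units, power = Φ(d/SE − 1.96) with SE = s·√(2/80).

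- Baseline as covariate: s = √(1 − 0.49) = 0.714, SE = 0.1129, power 83.2% (83.9% at d = 1/3).
- Change score: s = √(2(1 − 0.7)) = 0.775, power 76.9% (77.7%).
- Follow-up only: s = 1, power 55.1% (55.9%).

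Only the baseline-adjusted form gives more than 80%. As a cross-check, HbA1c (difference 0.5, SD 1.6, r = 0.7, alpha 0.025) with the same adjustment needs 100 per arm, and 100/(1 − 0.20) = 125, the stated size. The sample size reasoning is therefore that of baseline-covariate adjustment, and the PAL TEA figure needs both scores for each of the 80.

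**Step 2: delete those without baseline.** SE = √(2 × 0.51/(80(1 − m))).

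**Step 3: keep them through baseline as a response.** Those with both scores have residual variance 0.51. Those with follow-up only have variance 1. Approximately, SE = √(2/[80(1 − m)/0.51 + 80m]). This ignores what a 6-month score would add.

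For example, at m = 10% deletion leaves 72 per arm: SE = √(1.02/72) = 0.1190. Retention gives SE = √(2/(72/0.51 + 8)) = 0.1158.

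| Share without baseline | Left per arm after deletion | Power, deletion (d = 0.33 / 1/3) | Power, retention (d = 0.33 / 1/3) |
|---|---|---|---|
| 0% | 80 | 83.2% / 83.9% | 83.2% / 83.9% |
| 5% | 76 | 81.3% / 82.1% | 82.3% / 83.0% |
| 10% | 72 | 79.2% / 80.0% | 81.3% / 82.1% |
| 20% | 64 | 74.3% / 75.2% | 79.3% / 80.1% |

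**Step 4: where the claim fails under deletion.** The number per arm with both scores for 80% power is 2 × 0.51 × (1.96 + 0.842)²/d², which is 73.5 (so 74) at d = 0.33 and 72.1 (so 73) at d = 1/3. That allows 6 or 7 of 80 per arm to lack baseline (7.5% or 8.75%), so the claim is lost at roughly 8–9%.

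**Step 5: the simpler alternative.** Filling the baseline with the overall mean and adding a missing indicator, with one common residual variance, gives SE = √(2[0.51(1 − m) + m]/80). At d = 0.33 that is 81.5%, 79.7% and 76.3% power for m = 5%, 10% and 20%. It keeps everyone but recovers less precision than baseline as a response.

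**The case against.** **No affected participant is documented.** Recruitment was suspended in March 2020 and resumed in October 2020, and the sentence on people enrolled during these periods may mean those already in the trial, whose follow-up went remote. This stands: a reader might infer that baseline scores are known to be missing, and the article does not show it. Against that, Methods/design has recruitment under way in June 2020, the section on the COVID-19 impact questionnaires calls the October easing temporary, and recruitment runs to June 2024. The possibility is therefore real but unquantified.

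**Deletion is inferred.** The text does not say whether baseline is a covariate or a modelled response, nor what makes a case evaluable when baseline is absent, and an unseen analysis plan may settle this. That is fair, so the point is conditional. But baseline is listed beside strata and confounders, the tested times are all after baseline, and the power figure matches covariate adjustment. The article itself fixes the main analysis as evaluable-case.

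**Mitigation exists.** Multiple imputation is named for sensitivity analyses, and detectable differences are to be recalculated if the sample falls short. The first leaves the primary estimate unchanged; the second reports a loss without preventing it.

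**Stronger readings fail.** A reader might infer bias between arms, but a baseline lost to calendar restrictions is lost before allocation and cannot depend on arm. Nor is PAL TEA the primary outcome with least slack: HbA1c needs exactly the 100 per arm left after attrition, whereas PAL TEA needs 73–74 of 80. Scores at 18 months are not at stake, since the between-arm model stops at 12 months.

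**Conclusion.** The point holds in conditional form. The restriction rule covers the baseline visit, the article puts no baseline score in the way of randomisation, and the main model on its natural reading would exclude randomised participants who have 6- or 12-month PAL TEA but no baseline.

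The consequence is lost precision and an incomplete intention-to-treat set. Its size depends on an unknown share. At 5% missing the choice of method moves power by about 1 percentage point, at 10% by about 2 and at 20% by about 5; if no baseline was missed, nothing is lost. The documents do not support any particular share. These figures rest on the article's own d, r and 80 per arm, on a normal approximation, and on loss unrelated to the outcome.

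The point is worth acting on because a better main analysis is available at almost no cost, not because a large loss has been shown.

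**What to change.** 1. In the main between-arm model (3, 6 and 12 months where measured), keep participants with a missing baseline. Preferably model baseline as the first response with a common mean across arms. Otherwise, fill the baseline covariate with the overall mean and add a missing indicator, which is acceptable because the gap arises before randomisation. Apply this to PAL TEA and the other footnote-b outcomes.
2. Say what makes a case evaluable when baseline is missing.
3. Base the PAL TEA power statement on participants with usable data rather than 12-month completers alone, and report how many lack a baseline score.
4. Reconcile the June 2020 and October 2020 recruitment dates, and state whether any baseline visit was held without cognitive testing.

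The cost is wording and model syntax. No new data are needed, and with complete baselines the estimated effect is essentially unchanged.

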#### Device-based measurement of physical activity, sedentary behavior and sleep

Device-based measures of physical activity, sedentary behavior, sedentary behavior accumulation and sleep are collected using the activPAL4 activity monitor (PAL Technologies Limited, Glasgow, UK; default settings) worn on the thigh and the Actigraph GT3X+ (Actigraph, Pensacola, FL, USA) worn on the wrist. Both devices are intended to be worn 24 h per day for 10 days. Eleven days before their clinic visit, the activPAL4 — previously initialised and waterproofed with a nitrile sleeve — and the GT3X+ monitor and wrist band are sent to participants along with instructions and materials for affixing and wearing both devices (transparent polyurethane acrylate adhesive patches and wrist band, respectively). It has been previously shown that participants attaching their activPAL devices is feasible, acceptable, and results in adequate placement on the anterior midline of the thigh [41]. A sleep diary is provided to participants for 10 consecutive days to define sleeping and waking periods. Incomplete records for sleep and wake times are inferred from using one or more published methods (visual estimation; automated estimation; average values, for example with, Edwardson et al. [42]; Winkler et al. [43]; LaCroix et al. [44] respectively) and checked against movement visually.

The primary outcome of total daily sitting time (sitting or lying while awake and wearing the device, h/16 h day) will be derived from the activPAL4 data, as will secondary measures of physical activity, standing time, and sedentary behaviour accumulation. The activPAL4 uses triaxial accelerometry (30 Hz) and activPAL proprietary algorithms (here, VANE) to measure sitting/lying, standing, and stepping, stepping cadence, as well as transitions between sitting/lying and upright posture with high accuracy, reliability and excellent responsiveness to change for sedentary reduction interventions [45–48]. Further measures, with less published data on validity, are available using the CREA algorithm [49]. Relative energy expenditure will be estimated as metabolic equivalents (MET) from cadence [50] or acceleration [51] with a similar level of accuracy to most accelerometers. Consistent with standard procedures for the field [42], sleep time and device non-wear time (based on the daily log and device non-movement) will be excluded from measures of physical activity and sedentary behavior, as will days with insufficient wear. Sufficient-wear criteria for waking days will be 10h hours wear while awake, with evidence of movement (≥500 steps/day and not ≥95% of the day in any one activity). The activPAL data (activPAL VANE algorithm primarily) are processed in SAS (9.4 or higher) using a bespoke program adapted from previous studies [52]. Measures are extracted overall and for specific timeframes of interest identified from the log — work and non-work days, work and non-work times, and time at the workplace — and as detailed time-series data (daily; hourly).

The wrist-worn Actigraph GT3X+ activity monitor is used to estimate sleep duration (i.e., total sleep time) and sleep quality metrics (i..e, sleep efficiency, wakefulness after sleep onset, sleep onset latency) and also enables harmonisation of data to other studies that have used wrist-worn devices [53, 54]. Actigraph GT3X+ data are sampled at 30 hz. Behaviour classification from the raw wrist-worn accelerometer data is performed in GGIR, an open source R package [55]. This package implements methods providing valid and reliable estimates sleep duration and quality [56] as well as physical activity [57, 58] from wrist-worn devices. The 24-h wrist monitor data will be separated into sleep periods (for measuring sleep quality and duration) versus waking periods (for other measures) based on sleep and wake times collected in the online-administered daily logs. Sleep quality and duration measures exclude sleep periods during which the device is not worn, which will be identified via the Choi algorithm [59].

#### Clinical assessment

Clinic visits occur at every data collection timepoint, wth the exception being at 15 months. Prior to each visit, participants are reminded to abstain from engaging in any moderate- to vigorous-intensity physical activity, from consuming caffeine and alcohol in the 24 h prior to the assessment, to fast for at least 8 h, and to take their medications for the day of the visit at lunchtime during the visit rather than in the morning. For each clinic visit, participants report to the Baker Institute Clinic at 8 am. Over a 5-h period, participants have their body weight, body composition, blood pressure and vascular function assessed, a fasting blood collection, and undergo a 2 h oral glucose tolerance test (OGTT) during which they complete their questionnaires*.* Upon completion of the OGTT, participants receive lunch (e.g., sandwich/coffee) followed by cognitive assessments. Those participants whose assessment occurs during COVID-19 related social isolation mandates are emailed the questionnaires and referred to off-site pathology for glycosylated haemoglobin (HbA1c) testing, all other measures are omitted.

Clinic measures and their procedures are described below.

